### Data management

All data entered electronically will be range checked to ensure valid values. Any manually entered data will be double entered by two independent research assistants and then range checked for quality. Qualitative data will be audio recorded and then transcribed by a research assistant. All data are coded (de-identified) and stored on a secure server hosted by HIAS to which only the research team has access.

### Planned analyses

#### Quantitative data analysis

##### Descriptive analyses of baseline data

We will use descriptive statistics to characterize quantitative indicators of relevance, acceptability, and most indicators of feasibility. Descriptive statistics will include mean with standard deviation and/or median with interquartile range for continuous variables. Categorical variables will be displayed using frequencies and proportions. We will explore the distribution of demographic and psychosocial characteristics across the study communities and intervention conditions to characterize heterogeneity across sites and identify any major baseline imbalances between study conditions. We will calculate effect sizes to explore the magnitude of baseline differences between study conditions (Cohen’s *d* for continuous variables, Φ for categorical variables) and estimate the significance of this difference using mixed effects models accounting for clustering within communities and sites.

##### Psychometric analyses of baseline data

To evaluate the performance of participant-level outcome measure we will estimate the internal consistency, internal construct validity, and external construct validity (i.e., convergent) of these outcome measures. Internal consistency will be estimated using Cronbach’s alpha. Internal construct validity will be evaluated through confirmatory factor analysis and examination of model fit using Comparative Fit Index (CFI), Tucker-Lewis Index (TLI), root mean square error of approximation (RMSEA), and standardized root mean squared residual (SRMR). We will estimate the correlation among these participant outcome measures to investigator external construct (i.e., convergent) validity.

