### Outcomes

This feasibility trial aims to assess the appropriateness, acceptability, feasibility, and safety of implementing and evaluating *Entre Nosotras*, including when integrated with a stress management component, for migrant and host community women in Ecuador and Panamá. These outcomes will determine whether the study should progress to a definitive cluster-randomized comparative effectiveness trial and whether any research design or intervention adaptations are needed. These feasibility trial outcomes will be assessed using indicators and means of verification that are measured at the participant, service, and implementation level [29]. Table 2 details the outcomes, indicators that will determine progression to the definitive trial, means of verification, and assessment time points.

**Table 2 Tab2:** Study outcomes, indicators, and means of verification

Outcome	Indicator(s) for progression to definitive trial	Means of verification	Participants assessed	Time points			
				Screening/baseline	Intervention ***(5 weeks)***	Post-intervention	5-week follow-up
Appropriateness	**Eligibility:** > 50% of persons are screened are eligible	Routine study monitoring forms	Screened individuals	X			
	**Sensitivity to change:** Small to moderate within-group changes in outcome measures (*d* > 0.2)	Brief-COPE, K-6, OSS, PWI, WHODAS	Participants	X		X	X
	**Intervention fidelity:** > 75% fidelity to the intervention elements	Fidelity assessment^a^	Facilitator pairs		X		
	**Stakeholder perspectives:** Participants and facilitators report that the intervention and research procedures are appropriate and relevant to the needs of host and migrant women	Qualitative interviews	Participants, facilitators			X	X
Acceptability	**Intervention engagement and completion:** > 85% of participants attend first session; > 67% participants complete at least 4 sessions	Routine study monitoring forms	Participants		X		
	**Intervention usability:** Facilitators consider the intervention to have above average usability (IUS Score > 68).	Intervention Usability Scale	Facilitators		X		
	**Stakeholder perspectives:** Participants and facilitators report that the intervention and research procedures are acceptable and safe for host and migrant women	Qualitative interviews	Participants, facilitators			X	X
Feasibility	**Recruitment rate:** Average rate of enrollment is 5 women per week, at minimum, in each community	Routine study monitoring forms	Participants	X			

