	**Randomization:** No moderate to large differences (*d* > 0.5; Φ > 0.3) in baseline characteristics between study conditions within study sites	Demographics, Brief-COPE, K-6, OSS, PWI, WHODAS	Participants	X			
	**Attrition:** > 80% of participants complete baseline, post-intervention, and follow-up assessments	Demographics, Brief-COPE, K-6, OSS, PWI, WHODAS	Participants	X		X	X
	**Fidelity to research procedures:** No major protocol deviations	Routine study monitoring forms	Research assistants	X	X	X	X
	**Facilitator competencies:** An average score of > 2 on competency items, suggesting partially-fully demonstrating the competencies during intervention implementation	ENACT^a^	Facilitators		X		
	**Contamination:** Stress management components from the experimental conditions are included in all sessions for groups randomized to the enhanced intervention and none of the sessions for groups randomized to the standard intervention	Fidelity assessment^a^	Facilitator pairs		X		
	**Performance of outcome measures:** All outcome measures display adequate construct validity and internal consistency	Brief-COPE, K-6, OSS, PWI, WHODAS	Participants	X		X	X
	**Stakeholder perspectives:** Participants and facilitators report that the intervention and research procedures are feasible, adoptable, scalable, and sustainable. Participants and facilitators identify barriers and facilitators to implementation as well as strategies for overcoming/leveraging these factors.	Qualitative interviews	Participants, facilitators			X	X
Safety	**Adverse events:** Detected in < 10% of participants; no serious adverse events attributed to study participation	Adverse event reporting	Participants	X	X	X	X
	**Stakeholder perspectives:** Participants and facilitators report that the intervention and research procedures are acceptable and safe for host and migrant women	Qualitative interviews	Participants, facilitators			X	X

*Abbreviations*: *IUS* Intervention Usability Scale, *K-6* Kessler-6, *OSS* Oslo Social Support Scale, *PWI* Personal Wellbeing Index, *WHODAS* World Health Organization Disability Assessment Schedule

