##### Psychometric analyses of baseline and follow-up data

We will estimate sensitivity to change in participant outcome measures using mixed effects models within individuals, communities, and sites (i.e., within-group changes).

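### Table 2 assigns the measure-performance progression indicator to three time points, but its validity and consistency analyses are planned under baseline data only

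*Protocol article*

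**What the plan says.** The Outcomes section introduces Table 2 as giving, for each outcome, the "indicators that will determine progression to the definitive trial, means of verification, and assessment time points". Under Feasibility, the row on performance of outcome measures reads "All outcome measures display adequate construct validity and internal consistency". Its means of verification are the Brief-COPE, K-6, OSS, PWI and WHODAS. It is marked at screening/baseline, post-intervention and 5-week follow-up.

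The quantitative analysis plan has two adjacent psychometric sections:

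- The first is headed "Psychometric analyses of baseline data". It holds every analysis that serves this row: "Internal consistency will be estimated using Cronbach’s alpha", confirmatory factor analysis judged by four fit indices, and correlations among the measures for convergent validity.
- The second is headed "Psychometric analyses of baseline and follow-up data". Its only content is sensitivity to change: "We will estimate sensitivity to change in participant outcome measures using mixed effects models", fitted within individuals, communities and sites.

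Sensitivity to change is a separate progression indicator in Table 2, listed under Appropriateness: "Small to moderate within-group changes in outcome measures", with a threshold of d > 0.2.

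**The concern.** A progression criterion needs one clear statement of the data that decide it. Here the table points to three time points and the analysis plan to one. Suppose a scale has adequate alpha and factor structure at baseline but poor values after the intervention. Table 2 gives reason to count that against the measure. The analysis plan as written would not produce the later values, so nobody would see the problem.

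The later time points matter because the section on participant-level measures says the scales are being judged as possible effectiveness outcomes for the definitive trial, and effectiveness outcomes are read after the intervention as well as before it.

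**Working it through.** There is no stated statistical figure to reproduce. The check compares Table 2 with the analysis sections.

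**Step 1. What the marks in Table 2 mean.** Four rows that rely on the same five instruments can be compared.

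| Row in Table 2 | Baseline | Post-intervention | 5-week follow-up |
|---|---|---|---|
| Randomization (baseline balance) | X | – | – |
| Sensitivity to change | X | X | X |
| Attrition | X | X | X |
| Performance of outcome measures | X | X | X |

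All five instruments are given at all three assessments. If the marks only recorded administration, the Randomization row would carry three. It carries one. The marks therefore follow the data that each indicator uses. This reading also fits the baseline marks for sensitivity to change and attrition, since both need the baseline record.

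**Step 2. What is planned for the performance row.**

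| Analysis | Section where it is planned | Data named in the heading |
|---|---|---|
| Cronbach's alpha | First psychometric section | Baseline |
| Confirmatory factor analysis | First psychometric section | Baseline |
| Convergent correlations | First psychometric section | Baseline |
| Sensitivity to change | Second psychometric section | Baseline and follow-up |

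The fourth line belongs to another indicator, so it does not fill the gap.

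**Step 3. Count.**

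- Time points marked: 3. Time points with a planned validity or consistency analysis: 1. Unmatched: 3 − 1 = 2.
- Over five measures: 5 × 3 = 15 measure-by-time-point cells marked, 5 × 1 = 5 covered, 10 not covered.

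**Step 4. Data available later.** Inputs are the target of 220 women (Sample size section) and the retention criterion of more than 80% completing all three assessments (Table 2).

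- At the threshold, 0.80 × 220 = 176 women have complete data. Each later assessment on its own would have at least that many.
- For a standard error proportional to 1/√n, the loss of precision is √(220/176) = √1.25 ≈ 1.12, or about 12%. This takes n as the only thing that changes.

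The Sample size section justifies the factor analysis at 220, the full enrolled sample. That fits a baseline analysis and does not address the later time points.

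**The case against.** The strongest reply is that the marks show where source data come from and do not call for a verdict in each column. Change cannot be judged at baseline, yet the sensitivity row is marked there. The interview rows are marked at both later time points, although each selected person is interviewed once in that window. The indicator's own wording names no time point. This stands in part. A reader might infer that Table 2 requires adequate validity and consistency separately at every assessment, and the documents do not say so. It does not remove the conflict: on this same reading, post-intervention and follow-up data are sources for the performance row, and no analysis uses them for it.

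A second reply is that the section on feasibility of intervention and research procedures lists construct validity, internal consistency and sensitivity to change together, so the later marks may have been meant for the last of these. That is possible. But Table 2 gives sensitivity to change its own row with the same three marks, and the performance row names only the other two properties.

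A third reply is that headings in this article are loose. The descriptive section is also headed as baseline, yet it covers indicators such as attendance that arise later. That is fair, and the text under the first psychometric heading does not itself restrict the data. Still, the two psychometric headings sit side by side and differ precisely on whether follow-up data are used, so the restriction looks intended.

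Finally, an unseen analysis plan may add the later analyses. For that reason one cannot say that later performance will never be assessed, only that this article plans no such analysis. The conflict remains, because the article itself states both versions.

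**Conclusion.** The point holds as an internal inconsistency about a progression criterion. Table 2 assigns three time points to the performance of the measures, and the article plans the matching analyses for one. The gap is two time points for each of five measures. It rests on reading the marks as the data each indicator uses, which the Randomization row supports, and on taking the two psychometric headings at face value.

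The consequence is moderate. Baseline psychometrics on the full sample remain useful for choosing measures, and the criterion as worded could be decided on them if the authors say that is the intention.

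Three further inferences are tempting but are not established by the documents:

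- That the sessions change how women understand the items, so that the d > 0.2 rule would pick up a shift in meaning. The sessions do teach wellbeing and coping concepts, but no passage shows such a shift.
- That excluding women with high K-6 scores makes baseline a poor choice for psychometrics. This concerns one of five measures, and the article gives no figure for it.
- That omitting a longitudinal invariance check is an error. The article does not promise one, and such a check is optional.

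**What to change.** Run Cronbach's alpha, the factor model and the convergent correlations on the post-intervention and 5-week data as well as at baseline, and move them to a section whose heading covers all three. State which time points decide progression and how a measure is classed if it is adequate at one and not at another.

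Limit the factor-fit requirement to scales with a testable model. A one-factor model for the three-item OSS has 3 × 4 / 2 = 6 variances and covariances against 6 parameters (three loadings and three residual variances, with the factor variance fixed). That leaves no degrees of freedom, so its fit indices say nothing.

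The cost is a few more models on data already being collected, with somewhat lower precision at the later time points. If the baseline restriction is intended, the alternative is to remove the two later marks from the performance row, which needs no new analysis. An invariance check across time points may be added but is not needed to resolve the conflict.

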##### Psychometric analyses of baseline and follow-up data

We will estimate sensitivity to change in participant outcome measures using mixed effects models within individuals, communities, and sites (i.e., within-group changes).

### Qualitative data analysis

Process evaluation interviews will be transcribed and then coded and analyzed in Spanish using the Constant Comparative Method [56]. Within the primary domains of relevance, acceptability, and feasibility, the research team will develop concepts from the data through an iterative coding process. After a set of interviews, the research team will review and code the transcripts. They will discuss emerging themes and identified gaps to be further explored in the next set of interviews. This cycle will continue until the interviews are complete and the researchers agree they have achieved theoretical saturation [57]. The research assistants will then use the final codebook and review all transcripts to identify any overlooked concepts that contribute to themes that emerged at later stages of data collection and analysis.

### Ethics

All study procedures were reviewed and approved by the Institutional Review Board (IRB) at Columbia University Irving Medical Center (USA), Universidad de Santander (Panamá) and Universidad San Francisco de Quito (Ecuador).

#### Informed consent

Informed consent will be obtained by research assistants who completed training in human subjects research ethics prior to beginning the study [58]. Participants must provide verbal consent prior to screening. If eligible, participants then must provide written consent for enrollment prior to beginning the baseline assessment. Participants who are selected to complete the additional process evaluation interview are asked again to provide consent, including permission to audio record the interview. At all phases of the informed consent process and the research study, participants will be reminded that refusal to participate will not impact their ability to access services through HIAS or other agencies.

#### Harms

Data collection may be associated with minimal emotional discomfort due to the discussion of sensitive topics such as protection risks and psychosocial problems. We do not expect that the intervention or the assessments will lead to significant increases in distress. However, members of our research team are trained to identify acute signs of distress and to respond in a supportive manner and/or provide them with referral resources. At least one member of each of our research teams is a clinical psychologist and able to manage emergency situations. If participants require additional mental health or protection services, they will be referred to HIAS’ program staff in these sectors, respectively. HIAS has existing referral protocols in place to manage protection risks and mental health challenges.

We will adhere to local and national guidance regarding social distancing when completing the interviews and will not implement any in-person activities that do not comply with COVID-19 guidance. Participants who complete interviews remotely will be provided with a top-up on their airtime/data to cover the costs of communication during the interview. Participants who complete interviews in person will be reimbursed for transportation costs and provided a small snack.

#### Confidentiality

The intervention sessions will be conducted in groups, which increases the risk of breaching confidentiality. Facilitators will be trained to emphasize the importance of not sharing information about other women with people who are not part of the group. To preserve the confidentiality of women, we will ensure that efforts are made to protect the data, that the identifiable information collected is minimal, and that data collection forms are coded and do not include personally identifiable information.

#### Post-trial care

If we do not detect any risk or harms associated with the stress management component of the intervention, participants in the standard *Entre Nosotras* condition will be given a copy of the Doing What Matters in Times of Stress guide at the end of the intervention period. Overall, the trial is minimal risk. Referrals will be made to HIAS services, as needed, throughout the study period.

#### Protocol amendments

There are currently no protocol amendments to report. Any future amendments will be reported to the IRBs and clinicaltrials.gov.

## Discussion

The results of this feasibility trial will be used to determine whether we should progress to a definitive, fully powered trial evaluating the effectiveness and implementation of the *Entre Nosotras* intervention with and without a stress management component. Furthermore, this feasibility trial will provide preliminary evidence of the feasibility of using comparative effectiveness trials to optimize community-based psychosocial interventions in complex settings. If there are qualitative or quantitative indicators that suggest problems with relevance, acceptability, and/or feasibility of the intervention or study design, we will modify these procedures. We will also examine the validity and reliability of measures of psychosocial wellbeing, psychological distress, coping, social support, and functioning in Ecuador and Panamá as well as among migrant and host community women.

This feasibility trial and potential definitive trial to follow will advance the evidence for community-based psychosocial interventions in humanitarian settings. Consistent methodological challenges related to evaluating these interventions reveal the need for innovative interventions and evaluation approaches to fill this gap in evidence. The *Entre Nosotras* intervention aims to test an adaptable intervention model to which culturally specific and standardized components can be integrated to fit the population needs and operational context. The comparative effectiveness design may provide a foundation for future studies to disentangle the mechanisms by which specific intervention components improve psychological and social outcomes through adaptive and optimization study designs. Furthermore, this flexible intervention design and implementation approach may enable tailoring to different settings and understudied populations (e.g., gender, racial, and ethnic minorities) who may be underrepresented in the current study [59–61]. *Entre Nosotras* represents a novel, adaptable community-based psychosocial intervention that aims to empower migrant and host communities to collectively generate strategies and identify resources to improve the social and psychological dimensions of wellbeing among women in their community.

## Data Availability

Not applicable

## Abbreviations

ACT: Acceptance and Commitment Therapy
CFI: Comparative Fit Index
ENACT: Enhancing Assessment of Common Therapeutic factors
IRB: Institutional Review Board
IUS: Intervention Usability Scale
K-6: Kessler-6
MHPSS: Mental health and psychosocial support
OSS: Oslo Social Support Scale
PWI: Personal Wellbeing Index
RMSEA: Root mean square error of approximation
SRMR: Standardized root mean squared residual
TLI: Tucker-Lewis Index
WHODAS: World Health Organization Disability Assessment Schedule
